## Abstract

**Background:**

Walking, a closed kinetic chain (CKC) activity, is widely used in knee rehabilitation as it allows early weight bearing and movement. It has been suggested that retro-walking may provide additional benefits beyond those experienced by forward-walking. The present study will investigate the effect of retro- and forward-walking on quadriceps muscle strength, pain, function, balance and mobility in knee Osteoarthritis (OA) subjects.

**Methods/Design:**

Sixty-nine participants with knee OA will be recruited from the outpatient department in this randomized controlled trial. The participants will be randomly assigned to one of three groups; retro walking, forward walking or control group. The training program will be 3 days/week for 6 weeks. In addition, all the participants will receive a standard physiotherapy training program. An independent assessor blinded to group assignment will measure quadriceps muscle strength, knee pain intensity, functional disability, and mobility at baseline and 6 weeks after training.

**Discussion:**

The results of this study will enhance our understanding on the therapeutic effects of walking (retro- or forward-walking) in knee OA. The findings from this study will help determine whether retro- or forward-walking or both are effective in the rehabilitation of subjects with knee OA.

**Trial registration:**

Controlled Trials ISRCTN12850845, Registered 26 January 2015.

## Background

Knee osteoarthritis (OA) causes chronic disability in the older population worldwide [1, 2]. Its prevalence increases dramatically with age. Prevalence of radiographic OA is estimated at 80 % of all adults at or over the age of 65 years [3, 4]. The common impairments such as knee pain, decreased functional mobility, quadriceps strength, and stiffness leading to physical disability have been associated with knee OA [5–7].

In knee OA, the medial compartment is affected more often than the lateral. This may be due to higher load transfer through the medial compartment compared to the lateral, thereby producing higher knee adduction torque. A previous study suggested that the initial peak knee adduction torque during walking strongly predicted the severity and rate of progression of medial knee OA [8].

The focus of knee rehabilitation exercise has gradually shifted from open kinetic chain (OKC) to closed kinetic chain (CKC) exercises, which are more functional and could be safe and effective [9, 10]. In addition to increasing muscle strength, CKC exercise could also facilitate joint position sense [11–13]. Walking, a CKC exercise, is widely used in knee rehabilitation programs as it allows early weight bearing and mobilization. Published guidelines recommend regular walking exercises for individuals with knee OA [14]. Previous systematic review and meta-analysis reported moderate effects of walking on pain and function in people with knee OA [15]. Another study reported improved function following supervised walking and patient education with no adverse effects on OA related symptoms [16]. It has been suggested that retro-walking may provide additional benefits beyond those experienced by forward walking in healthy adult males and females [17, 18].

Retro-walking is considered a safe closed kinetic chain exercise since the compressive forces at the patello-femoral joint are reduced [19]. Retro-walking reduces quadriceps eccentric function, while the isometric and concentric quadriceps strength are preserved [20–22]. Retro-walking training programs have been found to increase quadriceps strength [22]. In addition, the cardiopulmonary demand is higher during retro- walking as compared to forward-walking [23, 24]. Therefore, these advantages make retro-walking a safe and effective component of rehabilitation programs.

Recently, Gondhalekar et al. [25] investigated the effects of retro-walking on pain and physical function in subjects with knee OA. They concluded that 3-weeks of retro-walking as an adjunct to the conventional training program significantly improved function in subjects with knee OA. Another study reported improved postural stability following long-term aerobic walking and weight training programs in subjects with knee OA [26]. In addition, Messier et al. [27] reported improved pain, disability, and performance following combined walking and weight training program in subjects with knee OA. Furthermore, Evcik et al. [28] reported improved pain, disability and quality of life following walking and home-based exercise in subjects with knee OA. In contrast, Toda [29] reported worsening of symptoms following a walking program in individuals with knee OA. However, the participants in this study were obese women with knee OA. Therefore, an increased intensity of pain in these participants may be due to the weight bearing nature of walking. The present study will investigate the effect of retro- and forward-walking in quadriceps muscle strength, pain, function, and mobility in subjects with knee OA.

### Hypotheses

The retro-walking training will reduce pain and improve quadriceps muscle strength, function, and mobility in subjects with knee OA.The forward-walking training will reduce pain and improve quadriceps muscle strength, function, and mobility in subjects with knee OA.The effects of the retro-walking will be greater compared to forward-walking in improvements of quadriceps muscle strength, pain, function, and mobility in subjects with knee OA.

## Methods/Design

### Trial design

This trial is a three-arm assessor-blinded randomized controlled trial (RCT) comparing retro-walking to forward-walking or control. All experiments will follow the Declaration of Helsinki. The protocol follows the CONSORT guidelines for reporting of non-pharmacological interventions [30].

### Participants

Sixty-nine participants with knee OA as per the American College of Rheumatology clinical and radiographic diagnostic criteria will participate [31]. In addition, participants must be between the ages of 40–70 years, have a body mass index (BMI) ≤ 29.9, and have a Kellgren-Lawrence radiographic grade of 1 –3 [32], as determined by the physician, to exclude end-stage knee OA patients. In case of bilateral knee involvement, the most symptomatic knee (as identified by the participant) will be evaluated. The participants will be excluded if they have a history of knee surgery to either knee within past 3 months, a systemic arthritic condition, any other muscular, joint or neurological condition affecting lower limb function, received physical therapy or an intra-articular injection in the knee within the past 3 months.

### Procedure

Figure 1 outlines the study phases. The participants who have knee OA and fulfilled inclusion criteria will participate in this study.

**Fig. 1 Fig1:**
[figure not shown]
Flow of participants through each stage of the randomized trial

## Interventions

### Standard physiotherapy program

All the participants will receive a supervised standard physiotherapy training program at the outpatient physiotherapy department as reported in a previous study [33]. The exercise program will comprise a combination of OKC and CKC exercises, including isometric quadriceps, terminal knee extension, isometric hip adduction exercise, straight leg raising exercise, leg press, and semi-squat. In a recent systematic review, Anwer et al. [34] reported the use of a combination of OKC and CKC exercises in the management of subjects with knee OA. All the participants will also receive Ultrasound therapy (1.5 W/cm2 for 7 min in continuous mode) around the knee joint before exercise. A previous study suggested that the continuous mode of therapeutic ultrasound is an effective and safe treatment modality in reducing pain and improving function in subjects with knee OA [35]. The participants will perform prescribed exercises for 6 weeks (3 days/week) as previously reported [33]. All the participants will be restricted to perform a home exercise or walking program other than the prescribed program.

### Retro-walking program

The participants in group A will undergo a supervised 10 min retro-walking training with 5 min of warm-up and cool down period for 3 days a week for 6 weeks on a flat surface at their comfortable speed along with a standard physiotherapy program as mentioned above. The participants will gradually increase the walking time up to 30 min over the period of 6 weeks. In the warm up and cool down periods, the subjects will perform ankle toe movements, hamstring and gastrocnemius-soleus stretching, and heel raise exercises.

### Forward-walking program

The participants in group B will undergo a supervised 10 min of forward-walking with 5 min of warm up and cool down periods for 3 days a week for 6 weeks on a flat surface at their comfortable speed along with a standard physiotherapy program as mentioned above. The participants will gradually increase the walking time up 30 min over the period of 6 weeks. In the warm up and cool down periods, the patients will perform ankle toe movements, hamstring and gastrocnemius-soleus stretching, and heel raise exercises.

### Control group

The participants in group C will receive only a supervised standard physiotherapy program as mentioned above.

### Outcome measures

Table 1 details the outcome measures that will be assessed to determine treatment effects. The primary outcome includes knee pain intensity and functional disability. The secondary outcome includes quadriceps muscle strength and functional mobility. All measurements will be taken at baseline (week 0), and at the end of the intervention (week 6).

**Table 1 Tab1:** Summary of outcome measures will be used to determine effectiveness of the treatment

Outcome	Measurement tool
Primary outcomes	
Knee pain	NRS, Reduced WOMAC pain subscale
Knee function	Reduced WOMAC physical function subscale
Secondary outcomes	
Isometric quadriceps muscle strength	Hand held dynamometer
Functional mobility	Timed up and go test

*NRS* numeral rating scale, *WOMAC* Western Ontario and McMaster Universities osteoarthritis index

### Measurement of quadriceps muscle strength

A Jamar hydraulic handheld dynamometer (Model, SH5001; SAEHAN, Changwon, South Korea) will be used to test quadriceps muscle performance. All the participants will be tested by the same physiotherapist. A test-retest reliability of therapist’s dynamometer testing will be established using 20 subjects over a period of 1 week. The participants will be instructed to sit at the edge of a treatment table with the knee in 600 of flexion using a standard goniometer. The lever arm length will be kept constant by placing the dynamometer close to the ankle at a point 80 % of the distance between the lateral malleolus and the lateral joint line of the knee. Each participant’s pelvis will be stabilized by a belt around the edge of the treatment table [36, 37].

The participants will perform four warm up contractions and will be asked to increase their knee extension force gradually over 3 s. The participants will be instructed to produce 50 % effort in the first three warm-ups and a maximal contraction on the fourth warm-up. After that, the participants will perform four maximal trials, and the average of the four trials will be used for the analysis.

### Measurement of pain intensity

Pain intensity will be assessed using a numerical rating scale (NRS) [38]. The participants will indicate their pain intensity on a scale of 0 to 10, with 0 (no pain) and 10 (worst pain).

### Measurement of functional disability

Functional disability will be assessed using the English version of the reduced Western Ontario and McMaster Universities Osteoarthritis Index (WOMAC). It consists of two dimensions: pain (five items) and function (seven items). The reliability and validity of the English version of the reduced WOMAC function scale have been established. There are two versions available one has a visual analogue response scale and the other a Likert five-point response scale [39, 40]. In the present study, a Likert five-point response scale will be used.

### Measurement of mobility by Timed Up and Go (TUG) test

The TUG test will be administered by one examiner in a quiet area [41]. A firm chair with arms (seat height of 46 cm) will be placed at one end and an object will be placed at the other end at a distance of 3-m. The test will begin with each participant sitting, back against the chair, arms on the lap, and feet just behind the starting-markings on the floor. The participants will be instructed as follows: “On the word ‘go’, stand up, walk comfortably and safely to the object at the end on the floor, walk around the object, come back, and sit all the way back in your chair.” Timing will start on the word “go” and ended when the participant returns to the chair, with back resting against the chair. A practice trial will be performed first and then followed by 2 recorded trials. The average of the 2 recorded trials will be used for data analysis.

### Adverse effects of the intervention

Adverse effects are defined as any increase in knee pain intensity perceived by the participants due to training protocol lasting for 2 days or more, or the participant requiring medications or consultation with the Physician. In addition, the risk of fall or injury to other body parts during training sessions will be considered as adverse effects. A senior Physiotherapist will supervise the entire training program.

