## Discussion

Recently, a Cochrane review reported the effects of land-based therapeutic exercise to reduce knee pain, improve physical function and quality of life in subjects with knee OA [42]. The effectiveness of walking programs on subjects with knee OA is not well known. In a previous study, Toda [29] reported worsening of symptoms following a walking program in subjects with knee OA. However, the participants in this study were obese women with knee OA. Therefore, an increased intensity of pain in these participants may be due to the weight bearing nature of walking. In contrast, another study reported improved postural stability following long-term weight training and aerobic walking programs in subjects with knee OA [26]. In addition, Messier et al. [27] reported reduced pain and disability after combined weight training and walking program in subjects with knee OA. Furthermore, Evcik et al. [28] reported the effectiveness of home exercise and walking program (forward-walking) in the management of subjects with knee OA.

Another study reported improved knee function following conventional treatment and retro-walking program in individuals with knee OA [25]. The results of the present study will enhance our understanding on the therapeutic effects of walking (retro- and forward-walking) in subjects with knee OA, and help determine whether retro- or forward-walking or both are efficacious in the management of subjects with knee OA. Thus, our study will assess both retro- and forward-walking program in subjects with knee OA. Previous studies were limited to pain and disability outcome measures; however, in the present study, we will assess quadriceps muscle strength and mobility, in addition to pain and disability, in subjects with knee OA [25, 28].

There will be some potential limitations to the present study. The present study will not assess a long-term follow up due to poor history of patients follow up in the current hospital setting. In addition, the age group of the participants will be restricted to 40–70 years. A previous study reported impaired cognitive function and severe pain in patients with knee OA, who were 70 years or older [43]. Furthermore, the authors reported an association between worse cognitive function with poor physical function in older adults with knee OA [43]. Another study reported increased risk of falls in older adults with knee OA [44].

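### The adverse-effect definition depends on perceived cause for pain and on session time for falls and injuries, so harm counts would not be comparable across the three arms

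*Protocol article*

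**What the plan says.** The section Adverse effects of the intervention gives an explicit definition with three parts.

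- **Pain:** "any increase in knee pain intensity perceived by the participants due to training protocol lasting for 2 days or more".
- **Medication or consultation:** "or the participant requiring medications or consultation with the Physician". No session limit is attached. The sentence does not settle whether the condition about training also governs this part.
- **Falls and injuries:** "the risk of fall or injury to other body parts during training sessions will be considered as adverse effects".

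Every arm has supervised sessions. The section Standard physiotherapy program, which applies to all participants, states: "The participants will perform prescribed exercises for 6 weeks (3 days/week) as previously reported". For the controls, "The participants in group C will receive only a supervised standard physiotherapy program as mentioned above". The retro-walking arm has walking on top of this: "The participants in group A will undergo a supervised 10 min retro-walking training with 5 min of warm-up and cool down period", and then "The participants will gradually increase the walking time up to 30 min over the period of 6 weeks". The forward-walking arm follows the same schedule.

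The section Outcome measures places all measurements at weeks 0 and 6 and does not list adverse effects among the outcomes. The section Statistical analysis describes no comparison of harms between arms. The trial is described as assessor-blinded, and nothing says that participants are blinded.

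**The concern.** Harms reported by arm in a three-arm trial will be read side by side, whether or not a test is planned. For that reading to be fair, an event has to be recorded in the same way whichever arm the participant is in. Two features of this definition work against that.

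First, a judgement about cause is part of what makes a pain flare an event. That judgement comes from people who know whether they are walking backwards, walking forwards or not walking. Second, falls and injuries are counted within a window, the training session, that is longer in two arms than in the third.

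A further fault is that the wording names a risk where it should name an occurrence.

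Tolerability is a live question here. The Background presents retro-walking as safe, and the Discussion cites a study in which symptoms worsened with walking. A pain flare that starts and resolves between weeks 0 and 6 does not show in the two scheduled pain assessments. This definition is the only route the article describes for capturing it.

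**Working it through.** The document states no adverse-event rate, count or safety margin, so there is no figure of the plan's own to reproduce. The check has three parts.

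**1. Added session time in the walking arms**

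Inputs from the intervention sections: 3 days a week for 6 weeks; walking starts at 10 min and reaches up to 30 min; 5 min is given for warm-up and cool-down. Assumption: the rise is linear across sessions (the article says only that it is gradual).

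- Sessions: 3 × 6 = 18.
- Mean walking time: (10 + 30) / 2 = 20 min, so 18 × 20 = 360 min.
- If the 5 min covers warm-up and cool-down together: 360 + 18 × 5 = 450 min = 7.5 h.
- If it is 5 min for each: 360 + 18 × 10 = 540 min = 9 h.

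The walking arms are therefore under session observation for about 7.5 to 9 h longer per participant than controls. The article does not give the length of the standard session, so the excess cannot be expressed as a ratio.

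**2. Effect of attribution on the pain count**

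This is an illustration on assumed inputs. Take 23 per arm (69 / 3, if allocation is equal) and a true flare risk of 20% in both arms.

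Counted flares = n × risk × share blamed on training.

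| Share blamed, retro-walking | Share blamed, control | Counted, retro-walking | Counted, control | Ratio |
|---|---|---|---|---|
| 80% | 40% | 23 × 0.20 × 0.80 = 3.7 | 23 × 0.20 × 0.40 = 1.8 | 2.0 |
| 60% | 60% | 2.8 | 2.8 | 1.0 |
| 40% | 80% | 1.8 | 3.7 | 0.5 |

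The ratio of counts equals the ratio of the attributed shares, whatever the common true risk. The document gives no information on those shares, so the distortion may be absent or may go either way.

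**3. What each part of the definition captures**

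| Event | Captured? |
|---|---|
| Pain flare of at least two days, blamed on training | Yes |
| The same flare, not blamed on training | Only if the medication or consultation part applies |
| Fall or injury in a session | Yes, if *risk of fall* is read as an actual fall |
| Fall or injury outside a session, with medication or physician contact | Unclear: depends on whether the condition about training governs that part |
| Fall or injury outside a session, with neither | No |

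**The case against.** The strongest reply is that the section is about adverse effects of the intervention, so tying events to training is a deliberate choice. The hypotheses, outcomes and analysis contain no safety comparison. A reader might infer that a planned comparison of retro-walking with control is biased. The documents do not support that, because no such comparison is described. What stands is narrower: counts collected under this definition would not be like for like once they are shown by arm.

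Four further points have force.

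- **Falls during the added walking are real harms of being assigned to it.** An excess of such falls would be a signal and should not be dismissed as an artefact of longer observation. The remaining problem is that controls' falls in the matching unsupervised time go unrecorded, unless the medication or consultation part applies.
- **Not every harm needs attribution or a session.** A reader might infer that falls between sessions are never counted. The medication or consultation part has no stated session limit and may catch some of them. Its scope is ambiguous, which is itself a reason to reword it.
- **A reader might call the fall criterion uncountable.** That fits only the literal wording. The evident intent is actual falls and injuries in sessions, which the supervising physiotherapist can count.
- **Pain is measured in all arms at weeks 0 and 6 without attribution.** Worsening that lasts to week 6 is therefore seen; a flare that resolves earlier is not.

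The remark in the Discussion that "Another study reported increased risk of falls in older adults with knee OA" follows the explanation of the age limit. Likewise, the Background's first use of *safe* concerns patello-femoral load. Neither sets a safety objective, and the point does not rest on them.

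A condensed article may leave the timing and wording of questions to the full protocol. The definition, however, is stated here, and it is the definition that needs changing.

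**Conclusion.** The point holds in limited form. As written, the pain criterion depends on attribution by participants who are not described as blinded. The fall and injury criterion depends on session time, which is about 7.5 to 9 h longer per participant in the walking arms under a linear increase. Falls and injuries outside sessions are missed unless an ambiguous third criterion applies. Harm counts by arm would therefore not be comparable.

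The documents do not show that any comparison will in fact be distorted. There is no event rate and no information on attribution, so neither the size nor the direction can be fixed. The twofold ratio in the illustration rests entirely on assumed shares of 80% and 40%. The *risk of fall* wording is a slip that is easily corrected. The change is still worth making, because the definition is the only described route for capturing transient harms and rewording it is cheap.

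**What to change.** Reword the definition so that the recorded events are:

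- any fall;
- any injury;
- any increase in knee pain that lasts at least two days;
- any resulting medication or physician consultation.

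Record them from randomisation to week 6, in or out of sessions and regardless of perceived cause. Ask about them in the same way in all three arms, at the existing sessions and at week 6. Keep perceived relatedness to training as a separate field, so that the treatment-related view the article intends can still be reported.

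This changes what is recorded, not how participants are managed. It needs a revised paragraph and a short standard question at contacts that already take place. The downside is that more events unrelated to training will be recorded.
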